# Impact of Virtual Care With Remote Automated Monitoring on the Rate of Acute Hospital Care Post Discharge and Index Length of Hospital Stay: Protocol for the Post Discharge After Surgery Virtual Care With Remote Automated Monitoring Technology 3 (PVC-RAM-3) Trial

**DOI:** 10.2196/72672

**Published:** 2025-06-02

**Keywords:** elective surgery, virtual care, remote automated monitoring, index length of stay, acute hospital care, randomized controlled trial

## Abstract

**Background:**

A substantial proportion of patients require acute hospital care after hospital discharge post surgery, and many regions and countries have surgical backlogs.

**Objective:**

The Post Discharge After Surgery Virtual Care with Remote Automated Monitoring Technology-3 (PCV-RAM-3) trial tests the hypothesis that informing surgeons and patients of virtual care with remote automated monitoring (VC-RAM) assignment will promote earlier discharge, thereby reducing the index length of hospital stay, and that postdischarge VC-RAM will reduce acute hospital care.

**Methods:**

The PVC-RAM-3 trial is a randomized controlled trial that compares VC-RAM to standard postdischarge care among 2500 adults undergoing elective noncardiac surgery in 3 Canadian hospitals. Following the randomization of patients prior to surgery, surgeons and patients are immediately notified whether the patient has been allocated to the VC-RAM or control group. Outcome adjudicators remain blinded to each participant’s group assignment. Patients in the intervention arm learn to use a Health Canada–approved cellular modem–enabled tablet computer and Bluetooth-enabled remote automated monitoring technology from Cloud DX to take daily wound photos for 7 days and measure daily vital signs (ie, blood pressure, heart rate, oxygen saturation, temperature, and weight) three times daily on days 1-7 and twice daily on days 8-14 post discharge, along with completing a brief recovery survey. Nurses review these data and conduct scheduled virtual visits (days 1, 3, 7, and 14). Nurses will escalate care to a preassigned and available perioperative care physician if predetermined vital sign thresholds are exceeded, concerning symptoms arise, or a medication error is detected. These physicians manage the issues and add or modify treatments as needed. The standard care group will receive postdischarge care as per the standard of care at the hospital where they undergo surgery. The coprimary outcomes are acute hospital care and the index hospital length of stay within the first 30 days after randomization.

**Results:**

Study recruitment and follow-up are completed, and analysis of the study results is underway.

**Conclusions:**

This trial will offer insights into the role of VC-RAM in reducing acute hospital care and index length of hospital stay among adults undergoing elective surgery.

**Trial Registration:**

ClinicalTrials.gov NCT05171569; https://clinicaltrials.gov/ct2/show/NCT05171569

**International Registered Report Identifier (IRRID):**

DERR1-10.2196/72672

## Introduction

Each year, more than 100 million adults (including >500,000 Canadians) aged 45 years and older undergo major surgery; of these, 29% develop prognostically important complications, 7.5% require hospital readmission, and >1.5% die within 30 days [1,2]. A Canadian Institutes of Health Information study analyzing 2.1 million acute hospitalizations found that surgical patients (both inpatient and same-day procedures) accounted for 31% of cases. Among the surgical cases, 7% had an unplanned 30-day readmission (costing CAD $9700 [US $6985.70] per readmission), and 19% returned to the emergency department within 30 days [3]. Overall, 20%-25% of adults discharged after elective surgery require acute hospital care within 30 days. With rising surgical volumes outpacing the growth of hospital bed capacity, surgical backlogs continue to grow [4,5]. Addressing these challenges requires innovative strategies to both shorten hospital length of stay (LOS) and reduce readmissions after surgery.

Virtual care with remote automated monitoring (VC-RAM) has emerged as a promising approach to improve postsurgical transitions to the home [6,7]. Virtual care encompasses all the ways that health care providers remotely interact (eg, telephone and tablet computer) with their patients. Remote automated monitoring (RAM) refers to the use of technology to remotely obtain data regarding patients’ biophysical parameters (eg, blood pressure) [6].

In our previous Post Discharge After Surgery Virtual Care with Remote Automated Monitoring Technology-1 (PVC-RAM-1) trial, 905 patients who had undergone nonelective surgery were randomized to VC-RAM for 30 days or standard care [8]. Patients in the experimental group used a cellular-enabled tablet and RAM technology that collected biophysical data, took wound photographs, and engaged in scheduled, and when needed, unscheduled virtual visits with nurses and physicians. There were threshold-based alerts that immediately triggered nurse-physician interventions to ensure the timely detection and management of abnormalities. We found a signal for ﻿the reduction in acute-hospital care (22% in the virtual care group vs 27.3% in the standard-care group; relative risk 0.80, 95% CI 0.64-1.01), brief acute hospital care (13.7% vs 18.1%; relative risk 0.75, 95% CI 0.56-1.02), hospital readmission (9.5% vs 12.8%; relative risk 0.77, 95% CI 0.53-1.11), and emergency department visits (19.7% vs 24.4%; relative risk 0.81, 95% CI 0.64-1.04) [8].

It is only credible to expect VC-RAM to impact outcomes if identified problems lead to a change in management. In PVC-RAM-1, centers could adjust the threshold parameters for care escalation. Post hoc analyses demonstrated that in the centers with the highest escalations of care (ie, centers where nurses identified, and physicians rapidly addressed abnormalities based on adherence to the predetermined vital sign thresholds), substantial absolute reductions in these outcomes were realized: acute-hospital care 14.1% (95% CI 5.2-23.0); brief acute-hospital care 11% (95% CI 3.6-18.4); and emergency department visits 14.2% (95% CI 5.4-23.0). However, these findings were post hoc and hypothesis-generating, requiring confirmation through an adequately powered trial. Additionally, the impact of advanced knowledge that a patient will receive VC-RAM on discharge timing and subsequent outcomes remains unclear.

The use of VC-RAM for patients discharged home after surgery can help identify and manage early postoperative complications. We hypothesize that this approach will reduce the need for acute hospital care, which includes hospital readmissions or emergency department visits after discharge. Additionally, we believe that if surgeons and patients know that postdischarge virtual care and RAM are available, they may be more inclined to opt for earlier discharges, potentially decreasing the length of the index hospital stay. To test these hypotheses, we are evaluating the impact of our VC-RAM intervention compared to standard postdischarge care on two coprimary outcomes: the rate of acute hospital care postdischarge and the index length of hospital stay.

By evaluating both acute hospital care and index LOS, this trial aims to build on lessons from PVC-RAM-1, extending to elective surgeries and providing evidence on integrating VC-RAM into routine postsurgical care. The goal is to optimize safe discharge and patient outcomes while addressing significant systemic challenges like bed capacity and surgical backlogs.

## Methods

### Design and Setting

The Post Discharge After Surgery Virtual Care with Remote Automated Monitoring Technology-3 (PVC-RAM-3) trial is a multicenter, parallel-group superiority randomized controlled trial involving 2500 patients undergoing elective noncardiac surgery at 3 Canadian hospitals: Hamilton General Hospital, Juravinski Hospital and Cancer Center, and St. Joseph’s Healthcare Hamilton. The trial evaluates the effects of VC-RAM compared to standard care post discharge. A study flow diagram is provided in Figure 1, and the SPIRIT (Standard Protocol Items: Recommendations for Interventional Trials) checklist is provided in Multimedia Appendix 1.

**Figure 1 figure1:**
[figure not shown]
Trial flow diagram. RAM: remote automated monitoring.

### Trial Population

Patients included in the trial are 18 years of age or older, undergoing inpatient elective noncardiac surgery with an expected hospital stay of ≤3 days after surgery, and provide informed consent. Exclusion criteria include the inability to communicate with research staff, complete study surveys, or undertake an interview using a tablet computer due to a language barrier or a cognitive, visual, or hearing impairment. Patients residing in areas without cellular network coverage are also excluded.

### Patient Recruitment

Study personnel use efficient recruitment strategies we previously developed in our perioperative trials, including identifying eligible patients through daily screening of surgical lists [8-10]. Surgeons with appropriate surgical populations (ie, surgeries with an anticipated LOS of 3 or fewer days) are contacted prior to any recruitment of their patients and asked to confirm their willingness to have their patients participate. Research personnel approach eligible patients during the preoperative period to obtain written informed consent (Multimedia Appendix 2).

### Randomization

Randomization occurs before surgery, after eligibility is confirmed, and informed consent is obtained. We randomize as close to the time of surgery as possible to minimize the risk of surgery postponement. Patients are randomized using an Interactive Web Randomization System, a 24-hour computerized system maintained by the coordinating center at the Population Health Research Institute, a joint institute of Hamilton Health Sciences and McMaster University in Hamilton, Ontario, Canada.

The randomization process uses block randomization with varying block sizes stratified by site, ensuring that study personnel and investigators remain unaware of block sizes. Patients are randomized in a 1:1 ratio to receive VC-RAM or standard care. Following randomization, research personnel notify the patient’s surgeon and the patient of the treatment allocation. Patients, health care providers, and data collectors are aware of treatment assignments, while outcome adjudicators remain blinded to treatment allocation.

### Trial Interventions

Patients are randomized to receive VC-RAM or standard care. Participating surgeons receive information on the trial protocol, objectives, and intervention model through rounds, in-service education, and discussions with trial researchers. This ensures that early discharge decisions for their patients are guided by their clinical judgment and understanding of the intervention care model (ie, when patients are assigned to the VC-RAM group, the patient will go home with VC-RAM to facilitate virtual care and vital sign monitoring).

The Cloud DX tablet is equipped with a camera and Bluetooth-enabled, Health Canada–licensed RAM technology (Figure 2). The Cloud DX Connected Health mobile app, hosted on the tablet, serves as the primary interface for the virtual care intervention and complies with the Personal Information Protection and Electronic Documents Act and the Personal Health Information Protection Act. This system has undergone extensive validation and user testing and was used in our previous PVC-RAM-1 trial [8,11]. The intervention begins the day after discharge and lasts 14 days or until 30 days post randomization, whichever comes first. The 14-day time frame is based on a period where major perioperative complications occur, and from our previous PVC-RAM-1 trial findings, where we determined that 30 days of monitoring often exceeds the needs of most patients [1,2,8]. Nurses establish contact and set up the system with patients as soon as possible after discharge, ensuring patients know how to seek help if they experience symptoms or issues arise.

**Figure 2 figure2:**
[figure not shown]
Cloud DX Connected Health kit. Cloud DX Connected Health kit, including Bluetooth-enabled Pulsewave wrist cuff blood pressure monitor, body weight scale, wireless oximeter, and temperature probe, paired with an Android health tablet. Reproduced with permission from Cloud DX.

Research staff teach patients (with family members participating where possible) in the VC-RAM group to use the automated Bluetooth-enabled monitoring devices paired with a preprogrammed, cellular modem–enabled tablet computer to measure their biophysical parameters, including blood pressure, heart rate, oxygen saturation, and temperature, three times daily on days 1-7 and twice daily on days 8-14. They measure their weight daily. They also complete a recovery survey developed for the trial, consisting of questions related to infection, bleeding, pain, dehydration, and cardiovascular and respiratory complications, daily. Patients photograph their wounds daily for the first 7 days unless otherwise directed. The biophysical parameters automatically upload via Bluetooth to the tablet, except for temperature, which is entered manually. These results are immediately wirelessly forwarded to the VC nursing team, and nurses actively review these results daily. If nurses do not receive a patient’s measurements, they will contact the patient at the earliest opportunity to understand the reasons behind the missing data. These vital signs, recovery surveys, and wound photos are parameters typically monitored in the hospital or during clinic visits, which we are now extending into the home setting.

Nurses conduct scheduled video visits on days 1, 3, 7, and 14 to assess symptoms, review wound photographs, reinforce recovery principles, and assess pain. They perform medication reconciliation on days 1, 7, and 14. Unscheduled video visits are arranged if biophysical measurements or survey responses exceed thresholds or if other health concerns are identified. Nurses escalate care to a preassigned physician when necessary, such as when RAM measurements exceed predetermined thresholds (examples in Multimedia Appendix 3), patients report specific symptoms (eg, shortness of breath), drug errors are identified, or concerns arise that require physician intervention. Physicians adjust treatments, order outpatient laboratory and diagnostic testing, liaise with surgeons, patients’ family physicians, or other health care providers, and arrange in-person clinic care when required.

Perioperative physicians hold scheduled video visits with patients on days 1 and 14 to assess patients, ensure proper medication use (by reviewing medication indications and proper dosing), and address medical needs. For patients who have a history of atherosclerotic disease, or are current smokers, an additional video call occurs on day 7 to optimize cardiovascular secondary prevention and smoking cessation therapy by ensuring that where indicated, patients were receiving secondary prevention medications (aspirin, statin, angiotensin-converting enzyme inhibitors/angiotensin II receptor blockers) and smoking cessation medications, respectively. These mechanisms ensure patients have 24/7 access to virtual nurses or physicians for urgent issues via secure video (Multimedia Appendix 4).

In both groups, discharge occurs when the most responsible surgeon deems it fit to discharge the patient. In the standard care group, patients receive postdischarge management according to the standard of care at the hospital where they underwent surgery. No changes to surgeons’ standard of care regarding postdischarge management occur for patients randomized to either group as a result of the trial. In Canada, standard postsurgery care typically involves follow-up with a health care provider within 30 days of discharge. Before this appointment, patients are responsible for contacting their surgeon or family physician with any concerns.

### Trial Outcomes

The PVC-RAM-1 trial provided encouraging data that virtual care with RAM may reduce acute hospital care [8]. In PVC-RAM-3, we wanted to inform the impact on acute hospital care and the index length of hospital stay. Initial sample size calculation assumptions suggested index length of hospital stay would require a larger sample size than acute hospital care. To avoid being underpowered by these outcomes, we made the index length of hospital stay the primary outcome. At the time of the final interim analysis, blinded overall data on the LOS and acute hospital care indicated there was adequate power to split the α and evaluate two coprimary outcomes (ie, acute hospital care and length of hospital stay). Consequently, we revised the primary outcome to include both index LOS and postdischarge acute hospital care as coprimary outcomes, making this change without any knowledge of the trial results.

The primary objective of this trial is to determine whether VC-RAM, compared with standard care after elective surgery, and informing surgeons and patients of VC-RAM allocation, reduces the occurrence of the coprimary outcomes within 30 days of randomization. The first coprimary outcome is postdischarge acute hospital care (defined as hospital readmission or emergency department visit) within 30 days after randomization. The second coprimary outcome is index hospital LOS (ie, time from the end of surgery to index hospital discharge).

Secondary outcomes during the first 30 days after randomization include (1) hospital readmission; (2) emergency department visit; (3) medication error detection; (4) medication error correction; (5) surgical site infection; (6) days in hospital; (7) pain of any severity, and moderate to severe pain assessed at 15 and 30 days after randomization; (8) proportion of patients with the atherosclerotic disease taking classes of efficacious medications at 30 days, (ie, an antiplatelet or anticoagulant drug, an angiotensin-converting enzyme inhibitor or angiotensin-receptor blocker, and a statin); and (9) the proportion of active smokers before surgery receiving pharmacological smoking cessation interventions at 30 days after randomization. Outcome definitions are presented in Multimedia Appendix 5.

Tertiary outcomes include (1) infection; (2) reoperation; (3) composite of myocardial infarction, acute heart failure, and arrhythmia that results in acute hospital care; (4) death; (5) health-related quality of life; and (6) health services usage–related costs.

We hypothesize that VC-RAM will reduce all primary, secondary, and tertiary outcomes, except for identifying more medication errors in the intervention group compared to the standard care group, which would reflect improved care through increased detection.

### Follow-Up

The day of randomization is day 1 of the trial, and all patients undergo 30 days of follow-up. Study personnel contact patients on day 30 to collect data on acute hospital care, secondary and tertiary outcomes, medication error detection and corrections, and current medications. The EQ-5D-5L is administered at baseline and day 30, and the Brief Pain Inventory-Short Form is administered on days 15 and 30. In the virtual care group, virtual nurses collect data on medication error detection and corrections throughout the intervention period.

If a patient reports an event, study personnel obtain source documentation from hospital or family physician records. If patients cannot be contacted directly, study personnel reach out to a designated relative, friend, or primary care physician. Study personnel and virtual nurses record all data in case report forms that are then entered into an electronic data capture system (Trial Master).

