For secondary and tertiary outcomes, we will use the chi-square test for binary or categorical variables and the 2-sample *t* test for continuous variables. We will assess the effect of VC-RAM using log-binomial regression models and report the corresponding relative risks and 95% CIs. For continuous outcomes, we will evaluate the intervention effect using analysis of covariance regression models to obtain effect estimates and their 95% CIs. Depending on the frequency of time-to-event outcomes, we may use the log-rank test to assess differences between groups. The α level for all secondary and tertiary outcomes will be set at .05. For the secondary and tertiary outcomes, we will not adjust for multiple testing as we will be evaluating the consistency of effect, number of outcomes, and size of the effect to offer insights into the reliability of any statistically positive secondary or tertiary outcomes. Economic analysis (Multimedia Appendix 7) will be done in a separate protocol and publication.

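### Binary pain outcomes at days 15 and 30: the named analysis has no baseline covariate although a baseline EQ-5D-5L is collected, so some precision is given away

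*Protocol article*

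**What the plan says.** Pain is secondary outcome 7 in the Trial Outcomes section: "pain of any severity, and moderate to severe pain assessed at 15 and 30 days after randomization". Two severity thresholds at two times read most naturally as four yes/no outcomes, although the outcome definitions themselves are in Multimedia Appendix 5, which is not shown.

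The Follow-Up section sets the instruments: "The EQ-5D-5L is administered at baseline and day 30, and the Brief Pain Inventory-Short Form is administered on days 15 and 30". It lists no baseline Brief Pain Inventory. Pain is also asked about in the recovery survey and at nurse visits, but only after discharge and only in the VC-RAM arm, so those data cannot serve as a baseline.

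For secondary and tertiary outcomes the Statistical Analyses section says "we will use the chi-square test for binary or categorical variables and the 2-sample" *t* test for continuous ones. On estimation it adds: "We will assess the effect of VC-RAM using log-binomial regression models and report the corresponding relative risks and 95% CIs". No covariate is named for these models. For continuous outcomes, by contrast, "we will evaluate the intervention effect using analysis of covariance regression models to obtain effect estimates and their 95% CIs". The threshold is common to all: "The α level for all secondary and tertiary outcomes will be set at .05", without multiplicity adjustment.

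The Randomization section stratifies by site alone, so baseline pain is not balanced by design.

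**The concern.** Some elective surgical patients have pain before the operation, and it is reasonable to expect that pain to carry into day 15 and day 30. A chi-square test cannot take a covariate, and the log-binomial model is described without one. The same paragraph names a covariate-adjusted method for continuous outcomes. As written, the binary pain comparisons therefore treat pre-existing pain as random noise, although the trial collects an instrument at baseline that could absorb part of it.

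What is at stake is precision: wider intervals and lower power for the pain results than the collected data allow. Recruitment and follow-up are complete, so a baseline Brief Pain Inventory can no longer be obtained, and the baseline EQ-5D-5L is the only comparative baseline measure in the article that could stand in for it.

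**Working it through.** The article gives no rate, standard deviation, correlation or power for pain, so there is no pain figure of the plan to reproduce.

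**Inputs**
- From the article: 1250 patients per arm (Sample Size Calculations); 1:1 allocation stratified by site (Randomization); α = .05 for secondary outcomes (Statistical Analyses).
- Assumed: control prevalence of the pain outcome 25% or 60%; relative risk 0.85; a five-level baseline pain item; latent normal correlation of 0.3 to 0.6 between baseline and follow-up pain.

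**Step 1: does leaving out the baseline harm validity?**
- The standard error of a chance imbalance in a baseline score is √(2/1250) = 0.04 SD, so the 95% range is ±1.96 × 0.04 = ±0.078 SD. The probability of an imbalance above 0.1 SD is 1.2%.
- For the share of patients with pre-existing pain, the 95% range is ±1.96 × √(2p(1−p)/1250): ±3.1 percentage points at p = 20% and ±3.9 at p = 50% (assumed prevalences).
- At the edge of the range, the follow-up score shifts by ρ × 0.078 SD: 0.016 SD at ρ = 0.2 and 0.047 SD at ρ = 0.6.
- The unadjusted test already allows for this variation. With a strongly predictive baseline and no treatment effect, 20,000 simulated trials gave a type I error of 5.3%. The Monte Carlo standard error is √(0.05 × 0.95/20,000) = 0.15 points, so this is compatible with 5%.

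The unadjusted comparison is therefore valid.

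**Step 2: how much precision is lost?**
The variance of the log relative risk standardised over the five-level item was compared with that of the unadjusted log relative risk, using 4000 simulated trials per scenario. Runs of 400 are too noisy: at latent correlation 0.5, batches of that size ranged from 6% to 22%. With v the proportional cut in variance, the interval narrows by 1 − √(1−v). A comparison that has 80% power unadjusted would have power Φ((1.960 + 0.842)/√(1−v) − 1.960).

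| Latent correlation (assumed) | Variance cut v | Interval narrower by | Power, if 80% unadjusted |
|---|---|---|---|
| 0.3 | 3%–6% | 1.5%–3.0% | 81%–82% |
| 0.4 | 8%–9% | 4.1%–4.6% | 83%–84% |
| 0.5 | 13% | 6.7% | 85% |
| 0.6 | 17%–22% | 8.9%–11.7% | 87%–89% |

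**Step 3: cross-checks**
- The usual approximation is v = ρ², where ρ is the correlation between the baseline value and the outcome as analysed. Coarsening to five levels and to yes/no lowers ρ below the latent value. At observed correlations of about 0.2 to 0.45 it gives 0.2² = 4% to 0.45² = 20%, in line with the table.
- A separate simulation with a continuous baseline score and logistic adjustment (1500 trials per scenario, 1250 per arm) raised power from about 76% to 77% at observed correlation 0.22, from 74% to 81% at 0.38, and from 75% to 85% at 0.50. The gain is negligible with a weak baseline predictor and useful with a moderate one.

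**The case against.** The strongest case against is that covariate lists are commonly left to the statistical analysis plan. That plan is not shown, this article is a condensed account, and a log-binomial model can carry covariates. This stands in part: a reader might infer that no baseline value will enter the pain comparison at all, and the article does not say that. It names no covariate and rules none out. What remains is that it does fix the test for binary outcomes, and a chi-square test is unadjusted by construction.

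A reader might also infer that a chance imbalance in preoperative pain would be misread as an effect of VC-RAM. Step 1 shows otherwise: the test and its interval already allow for it.

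It is also objected that the remedy relies on an EQ-5D-5L pain item that the article never describes. That is correct, and the item is stated here as an assumption.

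Finally, pain days run from randomization, and the rule in Statistical Analyses that drops events before surgery covers only the acute hospital care coprimary. A reader might conclude that pain scores taken before a postponed operation should be excluded. The documents do not support that as the main analysis. The share affected is not given, and the Randomization section says that patients are randomized as near to surgery as possible. Surgery date is also a post-randomization event in an open-label trial, so excluding on it conflicts with the intention-to-treat rule. It can be at most a sensitivity analysis.

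**Conclusion.** The point holds as one of efficiency. The stated analysis of the binary pain outcomes is valid but unadjusted as far as the article specifies it, and it leaves avoidable variance when a baseline EQ-5D-5L is available. The gain from adjustment is roughly 3% to 22% of the variance of the log relative risk.

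That range rests on assumed latent correlations of 0.3 to 0.6, assumed prevalences of 25% and 60%, and a five-level baseline pain item. The article supplies none of these. If only a summary EQ-5D-5L score is available, the gain depends on how well that score predicts later pain, which was not assessed.

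No stated figure is wrong, nothing is contradicted, and no bias or inflated error rate follows. It is a minor point about one of nine secondary outcomes, worth making because the remedy needs no new data.

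**What to change.** Before unblinding, specify in the statistical analysis plan:

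1. The baseline EQ-5D-5L pain/discomfort level enters as a covariate in the models for any pain and for moderate to severe pain at days 15 and 30. If item-level data are not available, use the baseline EQ-5D-5L score.
2. Report a marginal relative risk by standardisation, or use modified Poisson regression if the log-binomial model does not converge. Take the P value from the adjusted analysis, and keep the chi-square result as supporting.
3. Give absent baseline values their own category, so that no patient is dropped for lacking one.
4. Keep all randomized patients in the main analysis. At most, add a sensitivity analysis without pain scores taken before the index surgery.

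Confirm that the baseline questionnaire was completed before patients learned their allocation, since allocation is open and the article does not state the order.

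The cost is a few lines of plan text and code. The Abstract says that analysis is under way; if unblinding has already happened, label the adjusted result as post hoc and show it beside the unadjusted one.
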